### Sample size

The required sample size of 258 participants was calculated in the parent study [7], which will also be used in the current economic evaluation. Given the nature of our planned cost-effectiveness study, a sample size of 258 participants will be sufficient and relevant for conducting interviews to assess costs thus meeting the purpose of our study.

### Data

#### Cost data

The original research collected little cost data. Additional fieldwork will be conducted to supplement the cost data that will include cost data on human resources (family members and lay health supporters, and health professionals – village doctors, mental health administrators, and psychiatrists), intervention (text message development, and maintenance of texting platform and texting), project management, medication cost incurred due to increased adherence, and use of medical resources (outpatient and inpatient care), and indirect non-medical costs (efficiency at work and absenteeism at work in the past 4 weeks), assessed with the second part of the Trimbos/iMTA questionnaire for Costs associated with Psychiatric Illness (TiC-P) [21]. Primary data will be collected from the study participants by an interview and clinical data will be extracted from the medical records (Table 2).

**Table 2 Tab2:** Description of key model variables

Variables	Operational definition	Type of variable	Instrument used	Source of the data
*Demographic and epidemiologic variables*				
Population data	The initial number of people with a diagnosis of schizophrenia in each township	Continuous	Survey, records	Published literature, medical records, the 686 Program registry
Mortality rate	Incidence of death due to any reason	Continuous	Survey, records	Parent study, Medical record
Morbidity rate	Incidence of developing relapse	Continuous	Survey, records	Parent study, Medical record
Prevalence of Schizophrenia	National schizophrenia prevalence	Continuous	Survey, records	Published literature, China Health Statistical Yearbook
*Outcome variables*				
Medication adherence	The proportion of antipsychotic dosages taken over the past 30 days	Continuous	Unannounced pills count	Parent study, the 686 Program medication prescribing system
Relapse	Clinically significant exacerbation of psychotic symptoms	Dichotomous	Interview (self-report and/or caregiver report)	Parent study
Re-hospitalization	Re-hospitalization due to schizophrenia	Dichotomous	interRAI MH	Parent study, Medial record, field work
Functioning	Level of difficulty in accomplishing tasks and activities over the past 30 days	Ordinal	WHODAS 2.0	Parent study
Symptoms	Severity of psychotic symptoms	Ordinal	CGI-Sch	Parent study
*Program cost variables*				
Intervention cost	• Cost of training in preparation for LEAN • Cost of identifying individuals with schizophrenia • Cost of assessing medication adherence • Cost of message development and management • Cost of phones • Cost of texting to patients and lay-health supporters	Continuous	Cost estimating tool	Fieldwork to be conducted as part of the study, parent study
Human resource cost	Cost of family members, lay health supporters, and health professionals (village doctors, mental health administrators, and psychiatrists)	Continuous	Cost estimating tool	Fieldwork to be conducted as part of the study
Medication cost	Antipsychotics cost incurred due to increased adherence	Continuous	Cost estimating tool	Fieldwork to be conducted as part of the study
Indirect non-medical costs: • Efficiency at work Absenteeism at work	• Number of days with reduced efficiency due to feeling ill • Number of days absent from work	Continuous	TiC-P	Fieldwork to be conducted as part of the study

Parent study is the LEAN intervention

*interRAI MH* inter Resident Assessment Instrument-Mental Health, *WHODAS* World Health Organization Disability Assessment Schedule, *CGI-Sch* Clinical Global Impression in Schizophrenia, *TiC-P* Trimbos/iMTA questionnaire for Costs associated with Psychiatric Illness

Costs will be estimated using quantities of resource used and prices. The price will be estimated using existing market prices or shadow prices (the estimated price of a good or service for which no market price exists). Costs can be fixed (that cannot be changed) or variable (flexible and changes with productivity level); the sum of both these costs will be considered as the total cost. We will develop a standardized cost collection tool and will validate it before we collect new data. For the interpretation of costs of LEAN intervention, we will estimate the incremental change to total costs.

#### Effectiveness data

The effectiveness data will be extracted from published literature on risk-prediction. Published risk-prediction models will be used to estimate medication adherence [22] and the risk of developing relapses [23] and re-hospitalizations [24, 25].

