## Methods/design

### Study design

This will be a cost-effectiveness analysis (CEA) and cost-utility analysis (CUA) of a randomized controlled trial that will compare people with schizophrenia who received the 686 Program alone (control group) with those who received the LEAN intervention along with the 686 program (intervention group) that delivered mobile phone text messaging (Table 1). CEA, the most commonly employed type of economic analysis [14] will compare the costs of averting the number of relapses and the number of re-hospitalizations in LEAN intervention as compared to the 686 program. The added value of the LEAN intervention over the 686 Program will be captured through the incremental cost-effectiveness ratio (ICER). For CUA, the effects of an intervention will be expressed as a measure of ‘utility’, commonly measured using the quality-adjusted life-year (QALY) [14]. The study will adopt a broad societal perspective on value, specifically to incorporate all health care costs such as direct medical cost of identifying individuals with schizophrenia and their medication adherence, and all health effects such as patient symptoms, functioning, relapses, and re-hospitalizations [15]. The indirect non-medical costs will include production losses related to reduced efficiency at work and absenteeism at work [16].

**Table 1 Tab1:** Types of economic analysis and economic costs of the LEAN intervention

Type of analysis	Cost category	Costs	Outcome (effect)	Results expressed as:
CEA	• Cost of human resources • Cost of intervention • Cost of using medical resources	Monetary units (CNY)	Effect of intervention (number of relapses and re-hospitalizations averted	• Cost per relapse and re-hospitalization averted • ICER
CUA	• Cost of identifying individuals with schizophrenia and their medication adherence • Cost of assessing change in symptoms and functioning	Monetary units (CNY)	Healthy lifetime gained (QALYs)	Cost per QALY gained

*CEA* Cost-effectiveness analysis, *CUA* Cost-utility analysis, *CNY* Chinese yuan, *ICER* Incremental cost-effectiveness ratio, *QALY* Quality-adjusted life-year

The disease progression model as defined by McGorry et al. [17] that states different clinical staging of psychiatric disorders has been used to develop the basic design of the model. The final framework of the Markov model will be decided after the consultation with mental health experts, public health experts, and experts in economic modeling.

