### Study sample

Participants were randomly selected from the community-dwelling villagers having a primary diagnosis of schizophrenia in the parent study and were randomized 1:1 into two groups. Participants were selected if they were community-dwellers, were enrolled in the 686 Program, had a primary diagnosis of schizophrenia, were on oral psychotropic medications, and physically resided in 1 of 9 rural townships of Liuyang municipality. Participants were excluded from the study if they were hospitalized due to schizophrenia at the time of recruitment, had missed the most recent three consecutive past drug refills, or were physically incapable of using voice or text messaging. The primary outcome of LEAN trial was medication adherence assessed by unannounced home-based pill-counts; secondary outcomes included patient-level functioning assessed using 12-item World Health Organization Disability Adjustment Scale 2.0 (WHODAS 2.0) [18, 19], the severity of symptoms assessed by Clinical Global Impression in Schizophrenia (CGI-Sch) [20], relapse, and re-hospitalization. Outcome data were collected at baseline during the recruitment process and at 6 months after the implementation of LEAN. In addition to the outcome data collected as part of the trial, we will do additional fieldwork to collect program cost (i.e., cost data and effectiveness data) of the implemented LEAN intervention. Trained research assistants (RAs) will be responsible for conducting interview using survey questionnaire with the lay-health workers and family members to collect program cost data. RAs will also be responsible for obtaining the signed informed consent form from the participants. On the consent form, participants will be asked if they agree to use of their data and for permission for the research team to share relevant data with people from the university taking part in the research or from regulatory authorities, where relevant.

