### Outcomes

#### Effectiveness outcomes

The primary measure for cost-effectiveness will be the number of relapses and the number of re-hospitalizations avoided 6-month after the intervention. Relapses and re-hospitalizations cause a high burden to healthcare systems and patients and are used for different aims, such as a measure of cost control or quality of hospital care. There are no established criteria for defining relapse in schizophrenia. In our study, relapse will be defined as clinically significant exacerbation of psychotic symptoms evaluated by the investigators during interviews according to self-report or caregiver’s report [10]. The inter Resident Assessment Instrument-Mental Health (interRAI MH) assessment tool that has been validated in China will be used to assess the risk of re-hospitalization due to schizophrenia [26]. The interRAI MH includes a range of items measuring health service utilization, clinical and functional status, harm to self and others, social relationships, and vocational factors that assess the risk of re-hospitalizations [27, 28]. Study staff responsible for data collection will complete the assessment tool based on the interview, observation, and discussion with patients and family members. The study will also assess clinical/medical records to extract the data that will be valued in the model for predicting outcome measures. The secondary effectiveness measures will be medication adherence. The medication adherence will be measured using the proportion of dosage taken and good adherence will be defined as taking more than 80% of monthly pill counts, as stated in a previous study conducted among people with schizophrenia [29]. Adherence will be assessed using two unannounced home-based pill counts 30 days apart at the 6-month endpoint.

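### The Effectiveness data section takes adherence, relapse and re-hospitalization from published risk-prediction models, while Table 2 and the design take them from the randomised parent trial

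*Protocol article*

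**What the plan says.** The section headed Effectiveness data consists of two sentences. The first is "The effectiveness data will be extracted from published literature on risk-prediction". The second is more specific: "Published risk-prediction models will be used to estimate medication adherence [22] and the risk of developing relapses [23] and re-hospitalizations [24, 25". Neither mentions the trial, its arms, or any restriction to baseline risk or to the period after the trial.

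Other parts of the protocol point elsewhere:

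- Study design introduces the work as a "cost-effectiveness analysis (CEA) and cost-utility analysis (CUA) of a randomized controlled trial".
- Study sample says that participants were randomised 1:1, lists adherence as the parent trial's primary outcome and relapse and re-hospitalization among its secondary outcomes, and adds: "Outcome data were collected at baseline during the recruitment process and at 6 months after the implementation of LEAN".
- Table 2 (under Cost data) gives the source for adherence as "Parent study, the 686 Program medication prescribing system". For relapse the instrument is "Interview (self-report and/or caregiver report" and the only source is the parent study. For re-hospitalization the sources are the parent study, medical records and fieldwork.
- Effectiveness outcomes states: "Adherence will be assessed using two unannounced home-based pill counts 30 days apart at the 6-month endpoint".

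**The concern.** The protocol gives two incompatible answers to the question of where LEAN's effect comes from. An analyst working from the Effectiveness data section and one working from Table 2 would put different quantities in the denominator of the cost per relapse averted and the cost per re-hospitalization averted. Effectiveness outcomes names relapses and re-hospitalizations avoided as the primary cost-effectiveness measure.

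The two sources are not interchangeable. The trial supplies a contrast protected by randomisation. A published risk model supplies a risk for a patient with given characteristics. The second objective in Background is to compare LEAN with the 686 Program alone, and that calls for the contrast. Background also says that what the parent trial lacked was sufficient cost data; it reports effects on adherence, relapse and re-hospitalization as already shown.

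**Working it through.** No figure in the protocol can be reproduced here, because the question is which source feeds the calculation. The check sets the sections side by side.

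**Step 1. Source of each outcome.**

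| Outcome | Effectiveness data section | Table 2 source | Other sections |
|---|---|---|---|
| Adherence | published risk model | parent study; 686 prescribing system | trial primary outcome; pill counts at 6 months |
| Relapse | published risk model | parent study only | trial secondary outcome; judged by investigators at interview |
| Re-hospitalization | published risk models | parent study; medical records; fieldwork | trial secondary outcome; interRAI MH used to assess its risk |
| Functioning (WHODAS 2.0) | not mentioned | parent study only | Utility outcomes: basis of the QALYs |
| Symptoms (CGI-Sch) | not mentioned | parent study only | trial secondary outcome |

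Table 2 names published literature where it is meant, namely for the initial population and for national prevalence. It names it for none of the five outcomes. The row for relapse incidence also cites only the parent study and medical records. The conflict is therefore confined to the first three rows of the table above, and for those it is direct.

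**Step 2. What enters the ratio.** The protocol's formula is ICER = (CT − CC)/(ET − EC).

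- Under Table 2, with E counted as relapses or re-hospitalizations, ET − EC is the difference between the randomised arms.
- Under the Effectiveness data section, ET − EC is r(X in the LEAN arm) − r(X in the control arm). Here r is a published risk function and X is whatever it takes as input.

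In the second form, any difference between arms can arise only from differences in X, scaled by associations estimated elsewhere. That is not the randomised contrast. If adherence were the input that differs, an effect of LEAN on relapse by another route would not be counted. Background lists such routes: health education, monitoring for early signs of relapse, and linkage to primary care.

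**Step 3. Reach into the cost per QALY.** The ICER section defines its ratio per QALY. QALYs come from WHODAS 2.0, which Table 2 sources to the parent study, and the Effectiveness data section does not list them. There is an indirect path. The caption of Figure 1 attaches a cost and a QALY value to each Markov state, and Model development generates QALYs from that model. If modelled relapse or re-hospitalization risks set the transition probabilities, they also affect incremental QALYs and costs. The final model framework is still to be decided, so this path can be neither confirmed nor sized.

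**Step 4. Period covered.** The trial ran for 6 months. The Abstract sets the horizon at 1 year after the program ended, so 12 months of the horizon lie beyond the trial period. External information has a proper place there, but the Effectiveness data section does not confine it to that place.

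**Step 5. Size.** The protocol gives no relapse, re-hospitalization or utility values by arm and no predicted risks. Neither version of the denominator can be computed.

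**The case against.** The strongest reply is that a two-sentence section should not outweigh the rest of the protocol. Study design, Study sample, Table 2 and the pill-count rule all point to the trial, and a condensed article may simply have left unsaid that the risk models serve the longer-term simulation. Model development draws its parameters from literature, data synthesis and expert opinion, and Model validation compares modelled estimates with real-life results. This reply stands to the extent that the published models have a legitimate role. It does not remove the conflict, because the section states its rule without limit and under the heading where a reader would look for it. Nor is the section wholly isolated: Effectiveness outcomes also speaks of assessing the risk of re-hospitalization and of using records in a model that predicts outcomes.

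Three stronger readings are tempting and are not supported:

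- A reader might infer that every ICER loses its trial basis. QALYs are outside the section's list, and their source is the parent study.
- A reader might infer that the study has decided to discard the randomised effect and so cannot meet its second objective. Read as a whole, the protocol contradicts itself; it does not consistently drop the trial.
- A reader might infer that predicted risks must be equal in expectation in the two arms, giving a zero effect. That follows only if the models use baseline characteristics alone, which the protocol does not say. Inputs measured after randomisation, such as adherence or interRAI MH items, can differ between arms.

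**Conclusion.** The point holds as a contradiction about the source of the treatment effect on adherence, relapse and re-hospitalization. It is a stated rule that conflicts with other stated rules, so it is more than missing detail. Followed literally, it would replace the randomised contrast in the two cost-effectiveness ratios built on the primary measure. The cost per QALY is exposed only if modelled risks drive the Markov transitions. No magnitude can be given from the documents. The conclusion rests on one general premise: a risk-prediction model does not by itself identify the difference between two randomised strategies. It does not depend on the content of the cited models. The contradiction should be resolved before the analysis starts.

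**What to change.** Replace the Effectiveness data section with wording to this effect:

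> Between-arm effects on adherence, relapse and re-hospitalization over the 6-month trial are estimated by intention to treat from the participant data of the parent trial. These estimates and their standard errors enter the probabilistic sensitivity analysis. Published risk-prediction models are used only for baseline risk under the 686 Program alone, for extrapolation beyond month 6, and for external validation. The assumption made about the LEAN effect after month 6 is stated and varied in sensitivity analysis, for example effect maintained versus no further effect.

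The last sentence is needed because the trial data alone leave the LEAN effect undefined for the year after the program. Table 2 should then show the published models as a source for those limited uses. Because Study sample says that participants will be asked whether they agree to use of their data, the protocol should also say how those who do not agree are handled in the intention-to-treat estimate.

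The cost is a wording change and one additional set of scenarios. Study sample says that the trial outcomes have already been collected, so no new outcome data are required for the 6-month effects.

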### Outcomes

#### Effectiveness outcomes

The primary measure for cost-effectiveness will be the number of relapses and the number of re-hospitalizations avoided 6-month after the intervention. Relapses and re-hospitalizations cause a high burden to healthcare systems and patients and are used for different aims, such as a measure of cost control or quality of hospital care. There are no established criteria for defining relapse in schizophrenia. In our study, relapse will be defined as clinically significant exacerbation of psychotic symptoms evaluated by the investigators during interviews according to self-report or caregiver’s report [10]. The inter Resident Assessment Instrument-Mental Health (interRAI MH) assessment tool that has been validated in China will be used to assess the risk of re-hospitalization due to schizophrenia [26]. The interRAI MH includes a range of items measuring health service utilization, clinical and functional status, harm to self and others, social relationships, and vocational factors that assess the risk of re-hospitalizations [27, 28]. Study staff responsible for data collection will complete the assessment tool based on the interview, observation, and discussion with patients and family members. The study will also assess clinical/medical records to extract the data that will be valued in the model for predicting outcome measures. The secondary effectiveness measures will be medication adherence. The medication adherence will be measured using the proportion of dosage taken and good adherence will be defined as taking more than 80% of monthly pill counts, as stated in a previous study conducted among people with schizophrenia [29]. Adherence will be assessed using two unannounced home-based pill counts 30 days apart at the 6-month endpoint.

#### Utility outcomes

The measure for cost-utility will be Quality Adjusted Life Years (QALYs). QALY serves as a generic measure of health outcomes as it allows a combination of both morbidity, measuring the quality of life, and mortality, measuring the length of life, into a single score [30]. QALYs will be calculated using the 12-item version of the WHODAS 2.0 [18] that has been validated for the Chinese population [31, 32]. The WHODAS 2.0 measures daily functioning across six domains: cognitive (understanding and communicating), mobility (getting around), self-care, getting along with people, life activities and participation in society. Participants were asked to state the level of difficulty in accomplishing tasks and activities over the past 30 days, based on a 5-point ordinal scale (none, 1; mild, 2; moderate, 3; severe, 4; and extreme, 5) [33].

All data will be collected and managed using REDCap electronic data capture tool [34] hosted at the Sun Yat-sen University. To maintain confidentiality, all data collected as part of this study will be identified with the unique identification number allocated to the participants in LEAN trial.

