**Fig. 1 Fig1:**
[figure not shown]
Basic design of Markov model illustrating different states of mental health through which an individual with schizophrenia could transition. Each state is associated with the cost and value of quality-adjusted life-year (QALY) gained. All states may also progress to death or disability

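### QALYs are to come from the 12-item WHODAS 2.0, an ordinal functioning measure, and the plan names no conversion to a utility scale and no link to the Markov state values

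*Protocol article*

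**What the plan says.** All references are to the protocol article.

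- **What the cost-utility analysis needs.** Study design says the effect in the cost-utility analysis is expressed as a utility, commonly through the QALY. Utility outcomes adds that a QALY merges quality and length of life into one score.
- **Where the QALY comes from.** Utility outcomes fixes the source: "QALYs will be calculated using the 12-item version of the WHODAS 2.0". No other instrument is named for it.
- **What that instrument is, in the article's own words.** "The WHODAS 2.0 measures daily functioning across six domains". On the items: "Participants were asked to state the level of difficulty in accomplishing tasks and activities over the past 30 days, based on a 5-point ordinal scale", coded 1 (none) to 5 (extreme). The validation cited for the Chinese population is of the WHODAS 2.0 itself.
- **How it is listed as data.** Table 2 enters functioning as an ordinal variable with the parent study as its only source. Table 2 has no row for utility or health-related quality of life. Study sample lists the 12-item WHODAS 2.0 as a functioning outcome of the parent trial and gives the collection times as baseline and 6 months.
- **How the QALY is used.** It is the denominator of the ICER (section on the incremental cost-effectiveness ratio). It is also a property of each model state. The Fig. 1 legend says "Each state is associated with the cost and value of quality-adjusted life-year (QALY) gained" and adds that every state may lead to death or disability.

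**The concern.** A QALY is time weighted by a utility. The weight has meaning only on a scale where 0 stands for dead and 1 for full health, with distances between levels that reflect preferences. The article asks for a utility and then names, as its source, a measure that it describes as ordinal and about functioning. Two steps are missing between the score and the QALY:

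1. a conversion of WHODAS scores to a utility with those two anchors;
2. a rule that turns scores per patient, taken at two visits, into one value per Markov state, including dead.

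Without the first step the size of the QALY difference is a matter of convention. Without the second, the model has no defined QALY inputs. Every cost per QALY in the cost-utility analysis rests on both.

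**Working it through.** The article gives no utility, QALY or ICER figure, so there is nothing to reproduce. The check asks how far the ICER moves if the scores are simply rescaled.

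**Inputs from the article.** There are 12 items, each coded 1 to 5. A simple sum therefore runs from 12 × 1 = 12 to 12 × 5 = 60, a width of 48 points.

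**Assumed inputs, for illustration only.** The difference between groups is d = 3 points, held for T = 1 year. The incremental cost is ΔC = 1,000 CNY. The best score (12) has utility 1, and the worst score (60) has utility w, which the article does not fix.

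**Formulas.**
- Utility at score s: u(s) = 1 − (1 − w)(s − 12)/48
- QALY gain: ΔQALY = (1 − w) × d/48 × T
- ICER = ΔC/ΔQALY

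| Assumed w | ΔQALY | ICER (CNY per QALY) |
|---|---|---|
| −0.2 | 1.2 × 3/48 = 0.0750 | 13,333 |
| 0 | 1.0 × 3/48 = 0.0625 | 16,000 |
| 0.2 | 0.8 × 3/48 = 0.0500 | 20,000 |
| 0.4 | 0.6 × 3/48 = 0.0375 | 26,667 |
| 0.6 | 0.4 × 3/48 = 0.0250 | 40,000 |

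The range is 40,000/13,333 = 1.2/0.4 = 3-fold. This ratio depends only on the assumed range of w, because d, T and ΔC cancel. With d = 2 the ICER runs from 20,000 to 60,000, and with d = 5 from 8,000 to 24,000, again 3-fold. Since 1 − w is positive throughout, the sign of the QALY difference does not change.

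**Ordinal spacing.** Take a 3-point improvement as three items each moving one level, and let the loss of utility be the mean level weight over 12 items.
- Equal weights (0, 0.25, 0.5, 0.75, 1): the gain is 3 × 0.25/12 = 0.0625, wherever on the scale the items move.
- Assumed convex weights (0, 0.05, 0.2, 0.5, 1): three items from mild to none gain 3 × 0.05/12 = 0.0125, and three items from extreme to severe gain 3 × 0.5/12 = 0.125.

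The same sum-score change can thus be worth very different amounts, and an ordinal score alone cannot say which.

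**Link to the model.** Study sample gives scores per participant at baseline and 6 months. The Fig. 1 legend needs a value per state, and the Abstract sets the horizon at 1 year after the programme ended. No section says how the scores would be assigned to states. A score from living patients also does not say where dead lies on the scale.

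**The case against.** The strongest reply is that the article says the QALYs are calculated using the WHODAS 2.0, and this does not exclude a conversion. A journal article often leaves a scoring algorithm to a fuller plan. Model development also foresees literature review, data synthesis, health economists and a Delphi process for the parameters. Relapse and symptom data come from the same trial, so patient-level values could be averaged within states. Mortality is a listed model variable.

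Much of this stands. Several stronger statements that a reader might infer are therefore not supported:

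- **That the scores will be used directly, or that no preference weights or mapping exist for this instrument.** The article says neither, and the second cannot be settled from it. The arbitrary scale follows only if no conversion is applied.
- **That the probabilistic sensitivity analysis would hide the problem.** Analysis of uncertainty gives every model parameter a distribution. Utilities or mapping coefficients would be parameters, and nothing says that the scaling is held fixed.
- **That comparison with a threshold is the stated purpose.** The objective is LEAN plus the 686 Program versus the 686 Program alone. Background mentions willingness to pay as one factor in adoption decisions, and no threshold is given.
- **That a utility questionnaire could cheaply be given alongside the WHODAS.** Table 2 lists the WHODAS and CGI-Sch as parent-study data only, and that trial ran until June 15, 2016.

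What does not stand is that this is only omitted detail. The article chooses the QALY instrument and describes it as something other than a utility. The general account of parameter estimation does not mention utilities, so it neither supplies the missing step nor replaces the instruction in Utility outcomes.

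**Conclusion.** The point holds in this form: the plan fixes the QALY source as an ordinal functioning measure, names no conversion to a scale with dead at 0 and full health at 1, and does not connect patient-level scores to the state values of the Markov model. As written, the scale of the QALY is undefined.

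The consequence is conditional. If the scores are summed or rescaled, the cost per QALY can move about 3-fold through the anchor alone, for assumed worst-score utilities from −0.2 to 0.6. The CNY figures rest on an assumed cost, point difference and duration and predict nothing about this trial. Only the ratio carries over, and it rests on the assumed anchor range. Linear rescaling leaves the direction of the QALY difference unchanged. The cost-effectiveness analysis, whose primary measures are relapses and re-hospitalizations, does not use the WHODAS and is unaffected.

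**What to change.** In Utility outcomes, replace the sentence on the QALY source with one of two routes, fixed before the cost-utility analysis is run:

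1. **State utilities (the simpler route).** Attach published preference-based utilities to each Markov state, with dead = 0, and cite the source for each state.
2. **Mapping.** Name a validated mapping from WHODAS-12 to utility and apply it to the baseline and 6-month parent-trial scores. State how the mapped values are assigned to model states, because the horizon extends beyond the last WHODAS measurement.

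Under either route:
- add the utilities or mapping coefficients to the key inputs in Analysis of uncertainty, with distributions in the probabilistic analysis and ranges in the one-way analyses;
- add a utility row to Table 2;
- report WHODAS change as a functioning outcome, not as QALYs.

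The state-utility route is desk work, and neither route needs new data collection. The downside is that the utilities may come from other populations and that the uncertainty interval for QALYs will be wider.
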